### Analysis

Analysis will be by intention to treat which will include withdrawals and losses to follow up. There should be minimal differences in the baseline characteristics between groups due to the randomisation process. Statistical adjustment may be needed if important differences arise in baseline characteristics. Relative risks with 95% confidence intervals for the primary outcomes will be calculated. Measures of categorical data will be analysed with chi-squared tests and continuous data will be analysed with t-tests. Logistic regression and multiple linear regressions will be used if necessary to adjust for confounding for binary and continuous outcomes.

Risk will be controlled for in the statistical analysis and identified at the onset of labour rather than at enrolment in the study. Women will be categorised dichotomously as 'at low risk' and 'not low risk' according to maternal risk status at the time of the onset of labour. The risk factors and levels of risk are well defined in the ACM Guidelines [24] as level B or C - however, all definitions of risk will be available in the publication of the study.

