### Study Power

With 750 women or more in each of the intervention and control arms the study is powered (based on 80% power; alpha 0.05) to detect a difference in caesarean section rates of 29.4 to 22.9%; instrumental birth rates from 11.0% to 6.8%; and rates of admission to neonatal intensive care of all neonates from 9.9% to 5.8% (requires 721 in each arm). The study is not powered to detect infant or maternal mortality, however all deaths will be reported. Secondary outcomes will include rates of smoking cessation (eg 14.8% to 9.9% needing 747 women in each arm) and breastfeeding initiation and duration. We have calculated a sample to include a 30% attrition rate; therefore we aim to recruit a total of 1,950 women. All outcome measures identified by the Cochrane Protocol [19] will be collected. Individual hospital data bases and a purposefully designed data base will collect all primary and secondary outcome and process measures in addition to most cost outcome measures.

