### Group Allocation

The randomisation schedule will be prepared by a researcher not involved with treatment allocation. Following written informed consent from the woman, the research midwife will telephone the randomisation service. Details of the woman's consent and trial entry data will be recorded. The midwife will then be informed of the group (caseload midwifery or routine hospital care) to which the woman has been randomly allocated and the woman will be issued with a unique 4 digit study number. Study group allocation will be recorded on the Trial Register and Daily Log Book. To assess the comparability of the study groups, baseline demographic and medical information will be collected from the medical record at the time of entry into the study. Because the structure of practice is so different; there should be minimal opportunity for cross overs to occur. No attempt will be made to blind the identification of women randomised to either arm of the study.

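### Whether to adjust the primary outcomes is left to the observed baseline balance, and the named adjustment model does not by itself give the stated relative risk; fix an adjusted relative risk in advance

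*Protocol article*

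**What the plan says.** All of the analysis statements are in the Analysis section of the protocol article.

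- Effect measure: "Relative risks with 95% confidence intervals for the primary outcomes will be calculated". No adjustment is attached to this sentence.
- Trigger for adjustment: "Statistical adjustment may be needed if important differences arise in baseline characteristics". No threshold for importance and no covariate is given.
- Tool: "Logistic regression and multiple linear regressions will be used if necessary to adjust for confounding for binary and continuous outcomes". Nothing is said about returning from a logistic model to the relative-risk scale.
- One adjustment carries no condition: "Risk will be controlled for in the statistical analysis and identified at the onset of labour rather than at enrolment in the study".

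Under Group Allocation, "baseline demographic and medical information will be collected from the medical record at the time of entry into the study", so covariates measured before or at randomisation should be available. Under Study Power, 750 women per arm are planned "to detect a difference in caesarean section rates of 29.4 to 22.9" per cent, with 80% power and alpha 0.05.

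**The concern.** In a randomised trial, baseline differences arise by chance, as the Analysis section itself implies when it expects them to be minimal. Observed imbalance is therefore a poor guide to which covariates to use. A strong predictor of caesarean section adds precision even when it is balanced; a weak one adds almost nothing even when it is not.

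The rule also leaves a judgement until after the data are seen: which differences count as important, and whether adjustment is necessary. The trial is unblinded and lists seven primary outcomes (four maternal, three neonatal), so this freedom matters.

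Finally, if adjustment is triggered and the logistic coefficient is reported as it stands, the adjusted figure is a conditional odds ratio and the unadjusted figure a relative risk. For an outcome as common as caesarean section the two are not comparable.

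**Working it through.** **1. Reproduce the design figure.** Inputs from Study Power: p1 = 0.294, p2 = 0.229, 80% power, alpha 0.05 (taken as two-sided). With mean rate 0.2615,

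n = [1.96·√(2 × 0.2615 × 0.7385) + 0.8416·√(0.294 × 0.706 + 0.229 × 0.771)]² / 0.065² = (1.2181 + 0.5216)² / 0.004225, which rounds up to 717 per arm.

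The continuity-corrected version gives 747, against the stated 750, so the plan's figure is reproduced. Power at 750 per arm without the correction is 0.818.

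**2. Scale.**

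- Caesarean section: RR = 0.229/0.294 = 0.779; crude OR = (0.229/0.771)/(0.294/0.706) = 0.713. That is a 22% against a 29% reduction for the same data.
- Instrumental birth (11.0% to 6.8%): RR 0.618, OR 0.590.

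**3. How often chance sets off the trigger.** The article gives no threshold. Assume a difference counts as important at p < 0.05 and that covariates are independent. The probability of at least one is 1 − 0.95^k: 14% for k = 3, 23% for k = 5, 40% for k = 10.

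**4. Simulation at 750 per arm.** The control caesarean rate was 29.4%. Three covariates were used: two binary (one standing for site) and one continuous. Their prognostic strength is assumed, because the article gives none. There were 6,000 trials per setting under no effect and 3,000 under the design effect. Four analyses were compared:

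- unadjusted RR;
- a switch rule: logistic OR adjusted for any covariate differing at p < 0.05, otherwise unadjusted RR;
- a fixed adjusted RR from a standardised logistic model;
- free choice: significant if either the unadjusted RR or the fully adjusted OR is.

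Under the design effect:

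| Assumed R² | Variance of log RR, fixed ÷ unadjusted | Power, unadjusted | Power, switch rule | Power, fixed adjusted RR | Conditional OR |
|---|---|---|---|---|---|
| 0.015 | 0.99 | 0.820 | 0.821 | 0.826 | 0.710 |
| 0.079 | 0.93 | 0.822 | 0.824 | 0.847 | 0.694 |
| 0.17 | 0.83 | 0.816 | 0.825 | 0.877 | 0.668 |

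The marginal RR is 0.779 in every row, while the conditional OR moves with the covariates.

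Under no effect (type I error):

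| Assumed R² | Unadjusted | Switch rule | Fixed adjusted RR | Free choice |
|---|---|---|---|---|
| 0.015 | 0.051 | 0.051 | 0.051 | 0.058 |
| 0.079 | 0.052 | 0.048 | 0.047 | 0.061 |
| 0.17 | 0.052 | 0.047 | 0.048 | 0.068 |

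Monte Carlo standard errors are about √(0.05 × 0.95/6000) = 0.003 for type I error and √(0.82 × 0.18/3000) = 0.007 for power.

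**5. Interval width.** SE of the unadjusted log RR = √[0.771/(750 × 0.229) + 0.706/(750 × 0.294)] = 0.0877, so the 95% CI around 0.779 is 0.656-0.925. Multiplying the variance by 0.99, 0.93 and 0.83 gives 0.656-0.924, 0.660-0.919 and 0.666-0.911.

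**The case against.** **The unadjusted relative risk is a valid default, and a conditional rule is not in itself biased.** This stands. The mechanical switch rule held type I error at 0.047-0.051. A reader might infer that the trigger alone inflates the error rate; it does not. Only free choice between results did, and modestly. The wording leaves that choice open but does not say it will be used.

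**The article never mentions odds ratios.** Correct. Relative risks are promised without condition, and a logistic model can be standardised to a relative risk. A reader might infer that the plan commits to replacing the relative risk with an odds ratio; the text does not go that far. What stands is that the only named tool does not by itself give the stated measure. A labelled odds ratio is not wrong; it overstates the effect only if read as a relative risk.

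**Site is commonly left to the full protocol or analysis plan.** Agreed. The article lists no covariates, so its silence on site does not show that site is left out, and no criticism is made of that.

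**Adjustment might seem to rescue power lost to attrition.** A reader could note that 1,950 × 0.70/2 = 682 per arm gives caesarean power of 0.78, and that previous caesarean could restore it. The documents do not support this, for two reasons.

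- Mode of birth comes from hospital databases, so 30% of these outcomes need not be missing.
- The strength of that factor is unknown. R² = f(1−f)(q1−q0)²/(0.294 × 0.706), where f is the proportion with a previous caesarean, q1 and q0 the caesarean rates with and without one, and q0 = (0.294 − f·q1)/(1−f). Assuming f of 10-15% and q1 of 60-70%, R² is 5-14%. The Exclusions section removes women already scheduled for a planned caesarean at booking, which probably lowers both inputs. With f of 5-10% and q1 of 40-50%, R² is only 0.3-2.3%.

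**A later analysis plan could settle all this.** It could, but one faithful to the published sentences would keep the contingent rule.

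**Conclusion.** The point holds as a recommendation to change the stated method, not as a claim that the planned analysis is invalid. The choice of primary estimate is open after the data are seen, the adjusted result could be on a different scale from the unadjusted one (0.78 against 0.71 for caesarean section before any covariate effect), and most of the available precision is given up.

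The size of the gain is uncertain. Assumed R² of about 1-17% gives a variance reduction of about 1-17% and power of 0.83-0.88 instead of about 0.82 at 750 per arm. These figures rest on assumed covariate strength, and weak covariates would add almost nothing. The gain refers to a standardised (marginal) relative risk, not to the conditional log odds ratio.

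The case for fixing the rule does not depend on the gain being large. It is strengthened by the one unconditional adjustment in the section: risk status at labour onset arises after randomisation and may be affected by the model of care, so it does not belong in the adjustment set.

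**What to change.** In the Analysis section, replace the two conditional sentences with a fixed rule:

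- Each binary primary outcome is analysed with a relative risk and a risk difference, adjusted whatever the observed balance for site and a short fixed list of prognostic factors recorded at booking. Parity and previous caesarean are examples, if the entry data described under Group Allocation include them; the article does not name them.
- The model is modified Poisson regression with robust standard errors, or a logistic model standardised to the relative-risk scale.
- The unadjusted relative risk is reported alongside.
- The clauses that make adjustment depend on observed differences or on later need are deleted.
- Where risk status enters the adjustment set, it is the status at booking, not at labour onset.

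The cost is a few sentences and slightly more analysis work, with no new data collection if the chosen factors are already in the entry data. The downside is little gain if the covariates turn out to be weak.

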## Abstract

**Background:**

Australia has an enviable record of safety for women in childbirth. There is nevertheless growing concern at the increasing level of intervention and consequent morbidity amongst childbearing women. Not only do interventions impact on the cost of services, they carry with them the potential for serious morbidities for mother and infant.

Models of midwifery have proliferated in an attempt to offer women less fragmented hospital care. One of these models that is gaining widespread consumer, disciplinary and political support is caseload midwifery care. Caseload midwives manage the care of approximately 35-40 a year within a small Midwifery Group Practice (usually 4-6 midwives who plan their on call and leave within the Group Practice.) We propose to compare the outcomes and costs of caseload midwifery care compared to standard or routine hospital care through a randomised controlled trial.

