### Outcome measures

The *primary maternal outcomes *of the study are the proportion of women in each arm of the study:

• having caesarean section operations,

• instrumental births

• spontaneous vaginal births

• epidural analgesia for labour and birth

The *primary neonatal outcomes *of the study are the proportion of infants in each arm of the study who have:

• Apgar scores less than or equal to 7 at 5 minutes

• preterm birth (less than 37 completed weeks)

• admission to special care nursery or neonatal intensive care unit;

*Secondary maternal outcomes *include the proportion of women in each arm of the study who have:

• antenatal admissions

• induction and/or augmentation of labour

• women who are breastfeeding at six weeks and six months

*Cost outcomes *include:

• Comparative average cost per mother and baby episode as an AR-DRG

In addition to the primary outcomes listed above we will report on

*Other neonatal outcomes *including: low birth weight (less than 2500 g); length of neonatal hospital stay; neonatal convulsions; neonatal trauma (fracture or palsies); neonatal resuscitation: use of neonatal respiratory support (mechanical ventilation/CPAP) and/or perinatal mortality.

*Other maternal outcomes *include the rate of maternal complications (e.g. hypertension, ante partum haemorrhage, cord prolapse etc) and miscarriages in both the intervention and control arms; the proportion of women who have perineal trauma (episiotomy, 1st, 2nd, 3rd or 4th degree perineal tear, sutures required); postpartum haemorrhage (more than 500 ml or any amount which causes deterioration in maternal health; and/or blood transfusion); and serious maternal complications (e.g. intensive care unit admission or death).

*Although the study is not powered to detect other related outcomes including measures of perinatal mortality (e.g. fetal or neonatal death,) or maternal mortality, these events will be reported in full*.

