***INTERVENTION **Caseload Midwifery care: *Women allocated to the caseload intervention will receive antenatal, intrapartum and postpartum care from a named caseload midwife who will be backed up when necessary by other caseload midwives from within her Midwifery Group Practice. Each named caseload midwife works in a Midwifery Group Practice of four full time equivalent midwives each working a cycle of 152 hours during each four week period. Caseload midwives must be independent of the hospital rosters and employed on an annual salary to allow for workload to be self managed within each Midwifery Group Practice and responding to the needs of the women in their caseload. The named midwife is on call for the woman's labour and birth except in designated circumstances such as annual leave; sick leave; having more than one woman in labour; or if it is on one of the two days per week that the named midwife is scheduled to not work or be on call. Care will then be provided by a back-up caseload midwife from the Midwifery Group Practice. The caseload midwife is the woman's lead professional but one or more consultations with medical doctors may be part of routine practice [24]. Midwifery care is offered simultaneously with medical care if required. In addition to providing care until after the birth of the baby, the named caseload midwife (or a back up midwife from the Midwifery Group Practice) will attend the hospital on most days to provide some postnatal care until discharge and will provide full domiciliary care following discharge from hospital. Care will be provided according to hospital guidelines and protocols for up to six weeks following birth.

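### The planned tests treat twins as independent infants, which makes the neonatal intervals too narrow, and make no allowance for nesting under named midwives, which matters if midwives differ

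*Protocol article*

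**What the plan says.** The Analysis section names the methods. For tests: "Measures of categorical data will be analysed with chi-squared tests and continuous data will be analysed with t-tests". For estimates: "Relative risks with 95% confidence intervals for the primary outcomes will be calculated". Regression has one stated purpose: "Logistic regression and multiple linear regressions will be used if necessary to adjust for confounding for binary and continuous outcomes". Clustering by mother, midwife or group practice is not mentioned anywhere in the article.

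The unit for the neonatal primaries is the infant. Under Outcome measures, these outcomes "of the study are the proportion of infants in each arm of the study who have" a low Apgar score, preterm birth, or admission to special or intensive care. Exclusions lists only elective caesarean booking and an existing named care provider, so women with a multiple pregnancy can enter.

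On delivery of care, Definitions of Control and Intervention says: "Women allocated to the caseload intervention will receive antenatal, intrapartum and postpartum care from a named caseload midwife". Control women may see a different midwife at each visit. The Abstract gives the caseload: "Caseload midwives manage the care of approximately 35-40 a year".

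Study Power says: "With 750 women or more in each of the intervention and control arms the study is powered (based on 80% power; alpha 0.05", and the study is sized "to detect a difference in caesarean section rates of 29.4 to 22.9%; instrumental birth rates from 11.0% to 6.8" per cent. It contains no design effect.

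**The concern.** Two features of the trial conflict with the independence that these methods assume.

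**Twins.** Women are randomised, not infants, so a twin pair always shares an arm. Preterm birth is normally shared by the pair, so a chi-squared test on infants counts one event twice. The reported intervals for a primary outcome would then be narrower than the data justify. This needs no assumption about midwives and arises even if the model of care has no effect.

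**Midwives.** In the caseload arm a limited number of named midwives each look after many trial women. If midwives differ in their outcomes, those women are correlated, while control women have no lasting midwife. The Discussion claims evidence on the safety and effectiveness of a model of care. That reaches beyond the midwives who happened to take part, so variation between them belongs in the standard error. Left out, it could appear as an effect of the model, with more precision than is warranted.

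**Working it through.** **1. The plan's own figures.** Two-sided alpha 0.05 and 80% power are used (sidedness is not stated), with the standard two-proportion formula for independent observations and a continuity correction.

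| Outcome | Rates | Stated per arm | Recomputed, corrected | Uncorrected |
|---|---|---|---|---|
| Caesarean | 29.4 vs 22.9% | 750 | 747 | 717 |
| Instrumental birth | 11.0 vs 6.8% | 750 | 768 | 721 |
| Neonatal admission | 9.9 vs 5.8% | 721 | 723 | 675 |
| Smoking | 14.8 vs 9.9% | 747 | 747 | 707 |

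With the correction, all agree within 3%. The stated sizes are therefore independent-observation figures, and no allowance for clustering is hidden in them.

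**2. Twins, preterm birth.** The documents give no twin rate or twin risks, so all inputs are assumptions. Twin pregnancies are a fraction t of 1% or 2%, and the pair is fully concordant. Singleton risk is ps and twin risk is pt.

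- Overall infant risk: p = [(1−t)ps + 2t·pt]/(1+t)
- True variance per pregnancy: V = (1−t)[ps(1−p)² + (1−ps)p²] + 4t[pt(1−p)² + (1−pt)p²]
- Variance assumed by the test: V0 = (1+t)p(1−p)
- Inflation: D = V/V0
- True alpha: 2[1 − Φ(1.96/√D)]

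| t | ps, pt | p | V | V0 | D | True alpha |
|---|---|---|---|---|---|---|
| 1% | 7%, 7% | 0.0700 | 0.0671 | 0.0658 | 1.02 | 5.2% |
| 2% | 7%, 7% | 0.0700 | 0.0690 | 0.0664 | 1.04 | 5.5% |
| 1% | 7%, 55% | 0.0795 | 0.0833 | 0.0739 | 1.13 | 6.5% |
| 2% | 7%, 55% | 0.0888 | 0.1010 | 0.0826 | 1.22 | 7.6% |

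Correct intervals are wider by √D, that is by about 1% to 11%. The higher twin risk matters because a pair then departs from the overall mean together. The direction is the same for admission and Apgar score if twins resemble each other, but the documents offer nothing on which to base a figure.

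**3. Midwife nesting.** At 35-40 women a year over the 24 months of recruitment, a midwife could have at most 70-80 trial women, if every caseload place went to a trial participant. At 70 each, the 975 women recruited to the arm need 975/70 ≈ 14 midwives. If 750 are analysed across 14 midwives, m = 750/14 ≈ 54. A value of 35 allows for half the places going to other women. The ICC is not given; 0 to 0.02 is assumed.

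- Caseload-arm design effect: DE = 1 + (m−1)·ICC; control arm 1
- True alpha of the planned test: 2[1 − Φ(1.96/√((1+DE)/2))]
- Caesarean power of a valid test at n = 750: Φ(0.065/SE − 1.96), with SE² = [0.294·0.706 + DE·0.229·0.771]/750

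| ICC | m=35: alpha, power | m=54: alpha, power | m=70: alpha, power |
|---|---|---|---|
| 0 | 5.0%, 82% | 5.0%, 82% | 5.0%, 82% |
| 0.001 | 5.2%, 81% | 5.3%, 81% | 5.4%, 81% |
| 0.005 | 6.0%, 79% | 6.6%, 77% | 7.0%, 76% |
| 0.01 | 7.0%, 76% | 8.1%, 73% | 9.1%, 71% |
| 0.02 | 9.0%, 71% | 11.3%, 65% | 13.2%, 61% |

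Example, m = 70 and ICC 0.02: DE = 1 + 69·0.02 = 2.38; √(3.38/2) = 1.30; alpha = 2[1 − Φ(1.96/1.30)] = 13.2%. SE = √[(0.2076 + 2.38·0.1766)/750] = 0.0289; power = Φ(2.247 − 1.96) = 61%. A pooled critical value lowers the power figures by up to 1.5 points.

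A beta-binomial simulation (200,000 trials per setting, caesarean rate 29.4%) agreed with the alpha formula. For ICC 0.005, 0.01 and 0.02 it gave 6.0%, 6.9% and 9.0% at m = 35.

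**The case against.** The strongest objection is to a reading that a reader might infer: that the real false-positive rate exceeds 5% for every primary outcome, because 70-80 women share each midwife. The documents do not support that.

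- The midwife effect depends on an ICC that is not given. At 0 the error rate is 5.0%, and at 0.001 about 5.2-5.4%. Under a null in which neither arm nor midwife affects any woman, individual randomisation keeps it at 5%. Inflation needs real differences between midwives and inference beyond those in the trial.
- The figure of 70-80 is stated nowhere and is an upper bound. Trial Recruitment describes caseload care as something the hospital offers, so other women may fill places. Back-up midwives cover leave, concurrent labours and off-call days, which dilutes any one midwife's influence.
- Nesting in one arm only is a modelling assumption. Control women are booked under the consultant on call and may share a GP, which are groupings too.

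All of this stands and makes the midwife part conditional. It does not reach the twin part, which needs only similarity within pairs.

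On twins, the fair objection is that the size rests on outside assumptions and is small if twins carry singleton risk. That also stands, and is why a range is given.

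Finally, an article condenses, and an unseen SAP could specify robust variance. But the text does not merely stay silent: it names chi-squared tests for categorical data and reserves regression for confounding, and the sample sizes already assume independence. What is written should be corrected.

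**Conclusion.** The point holds in two parts of different strength.

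**Twins: a definite flaw in the stated method, modest in size.** The intervals for infant-level primaries are too narrow. For preterm birth the true type I error is about 5.2-5.5% if twins have singleton risk and 6.5-7.6% with 7% and 55% preterm birth. Both ranges assume 1-2% twin pregnancies and full concordance. Caesarean, instrumental birth, spontaneous vaginal birth and epidural use are not affected.

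**Midwives: conditional.** If midwives differ and the conclusion is about the model of care, 35-70 trial women per midwife and an ICC up to 0.02 put the type I error between 5% and about 9-13%, and caesarean power between 82% and about 71-61%. The documents do not show where in that range the trial lies, and the lower end is no inflation at all. What can be said firmly is that neither the tests nor the sample sizes allow for this nesting.

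**What to change.** 1. In Analysis, specify that infant outcomes are analysed with variance clustered on mother, by GEE or by modified Poisson regression with robust standard errors, which still yields relative risks. The cost is a few lines of code and slightly wider intervals.
2. Record the named midwife allocated to each caseload woman. Group Allocation describes recording the study group only, so this is one extra data field.
3. Prespecify a partially nested sensitivity analysis for the women's outcomes: a random midwife effect in the caseload arm, a small-sample correction, and the ICC reported. With few midwives the ICC will be imprecise, which is why this is proposed as a sensitivity analysis and not as the primary one.
4. In Study Power, state that the figures assume no clustering by midwife, and show how power changes over a plausible range of ICC and caseload size. This costs a sentence.

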### Aims and Objectives

The aim of the study is to compare the outcomes and costs of caseload midwifery care compared to standard or routine hospital care for childbearing women through a randomised controlled trial.

**Primary objectives **are to determine whether women receiving caseload midwifery care experience the same rates of caesarean section, instrumental births and use of epidural analgesia compared to women receiving routine care and to determine whether women with identified risk factors at the onset of labour experience the same rates of neonatal morbidity (including admission to the neonatal intensive care unit), and perinatal mortality compared to routine care.

We will determine whether caseload midwifery care costs the same as routine maternity care and whether women who receive caseload care experience the same potential benefits and consequences of postnatal care as women receiving routine maternity care.

**Secondary objectives **are to determine whether midwives offering caseload practice experience the same levels of work satisfaction and the same levels of productivity as midwives working in conventional rostered and rotating shifts; and to determine whether obstetricians working with caseload midwives experience the same levels of professional satisfaction as obstetricians working with rostered midwives in the routine work setting. We will also determine the rates of postnatal depression and smoking in pregnancy.

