#### Trial Eligibility

Women will be eligible for trial entry if they are less than 24 completed weeks of pregnancy and a minimum of 18 years old at booking in. At the participating centres research midwives will recruit the required number of women in the experimental arm over 24 months. We will enroll 1950 women in anticipation of no more than a 30% attrition rate.

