#### Exclusions

Women will be excluded from the trial if they are electively booked to give birth via caesarean section at the time of booking in; or are already booked with a named care provider (Obstetrician/GP/midwife).

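### Risk adjustment is fixed on status at labour onset, after randomisation and antenatal caseload care, so the risk-controlled estimate and one primary neonatal objective are open to bias

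*Protocol article*

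**What the plan says.** The Analysis section of the protocol article makes the choice outright: "Risk will be controlled for in the statistical analysis and identified at the onset of labour rather than at enrolment in the study". The variable has two levels, low risk and not low risk, assigned "according to maternal risk status at the time of the onset of labour" using the ACM Guidelines levels B and C. The same section plans intention to treat, risk ratios with 95% intervals for the primary outcomes, chi-squared tests, and regression where needed for confounding. It does not say whether the unadjusted or the risk-controlled result is the primary one.

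Four other sections bear on this:

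- **Trial Eligibility:** "Women will be eligible for trial entry if they are less than 24 completed weeks of pregnancy".
- **Definitions of Control and Intervention:** caseload women "will receive antenatal, intrapartum and postpartum care from a named caseload midwife".
- **Exclusions:** among women planning caesarean, only those "electively booked to give birth via caesarean section at the time of booking in" are kept out.
- **Aims and Objectives:** one primary objective is "to determine whether women with identified risk factors at the onset of labour experience the same rates of neonatal morbidity", together with perinatal mortality.

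**The concern.** A covariate used to adjust a randomised comparison should be fixed before allocation. This one is not. Between randomisation and labour the two arms receive different antenatal care, and the article treats what happens in that interval as an outcome: Outcome measures lists "the rate of maternal complications (e.g. hypertension, ante partum haemorrhage, cord prolapse etc) and miscarriages in both the intervention and control arms". Complications of that kind may well feed into risk status at labour onset. They cannot be both an effect of care and a confounder to be removed.

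Three things follow.

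1. If caseload care changes the share of women who are not low risk, adjustment takes that part of the effect out of the estimate.
2. If unmeasured factors affect both risk status and the outcome, the arms are no longer balanced on them within risk strata.
3. A woman delivered by caesarean before labour has no labour onset and so no stated category, yet she counts in the first primary outcome.

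The neonatal objective has the same weakness, because membership of its subgroup may depend on the arm. The unadjusted whole-arm comparison does not answer that objective.

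**Working it through.** **Order of events.** Randomisation comes before 24 weeks, then antenatal care by arm, then risk classification at labour onset, then birth outcomes. The adjustment variable lies between allocation and outcome.

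**The plan's own figure.** For caesarean section at 29.4% against 22.9% (Study Power), two-sided alpha 0.05 (sidedness assumed), 80% power and equal arms, the two-proportion formula with continuity correction gives 747 per arm. The article states 750. Without the correction it gives 717, and power at 750 is 82%. The planned total relative risk is 0.229/0.294 = 0.779. The sample size is not in dispute.

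**Illustration 1: a shift in risk status.**

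- From the article: 29.4%, 22.9%, 750 per arm.
- Assumed: 50% of controls are not low risk, with caesarean risks of 15% (low risk) and 43.8% (not low risk), so that 0.5 × 15% + 0.5 × 43.8% = 29.4%. The relative risk is the same in both strata. Every woman has a category.

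Let q be the share of caseload women who are not low risk. To keep the total at 22.9%, the within-stratum relative risk must be r = 0.229 / [(1 − q) × 0.15 + q × 0.438]. This r is what the risk-adjusted analysis estimates.

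Power is for a stratified test with weights w = n0·n1/(n0 + n1), z = Σw·d / √(Σw²·V), power = Φ(z − 1.96). Here d is the risk difference in a stratum and V its variance.

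| q | denominator | adjusted RR | power at 750 per arm |
|---|---|---|---|
| 55% | 0.3084 | 0.74 | 95% |
| 50% (no shift) | 0.2940 | 0.78 | 85% |
| 48% | 0.2882 | 0.79 | 79% |
| 45% | 0.2796 | 0.82 | 67% |
| 40% | 0.2652 | 0.86 | 42% |

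Example at q = 45%: r = 0.229/0.2796 = 0.819. In the low-risk stratum w = 375 × 412.5/787.5 = 196.4 and d = 0.15 × 0.181 = 0.027. In the other, w = 375 × 337.5/712.5 = 177.6 and d = 0.438 × 0.181 = 0.079. Then Σw·d is about 19.4, √(Σw²·V) about 8.1, z about 2.40, and power Φ(0.44), about 67%. The log effect lost is 1 − ln 0.819/ln 0.779, about 20%.

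The total effect is 0.78 in every row; only the adjusted figure moves.

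**Illustration 2: an unmeasured common cause.** Assume no effect of care on caesarean at all (true relative risk 1.00) and an unmeasured factor present in half of women that raises not-low-risk status by 30 points and caesarean by 20 points. If caseload care lowers not-low-risk status by 5, 10 or 20 points, the adjusted relative risk is 1.01, 1.02 or 1.05.

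**Illustration 3: women without labour left out.** The article does not say this would happen. If it did, the relative risk among labouring women would be [(0.229 − b)/(1 − b)] / [(0.294 − a)/(1 − a)], where a and b are the assumed pre-labour caesarean rates in control and caseload.

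- a = 12%, b = 8%: 0.162/0.198 = 0.82, power about 40% starting from 750 per arm.
- a = 14%, b = 8%: 0.162/0.179 = 0.90, power about 13%.
- a = b = 12%: 0.124/0.198 = 0.63, an exaggerated effect.

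**The case against.** The strongest reply is that the section also plans intention to treat and relative risks for the primary outcomes. An unadjusted relative risk is untouched by any of this, so the problem may affect only one of two planned analyses. That stands as a limit on scope. It does not remove the defect: the statement that risk will be controlled for carries no condition, neither estimate is named primary, and the two could disagree once the data are in.

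A second reply is that bias is possible, not established. That also stands. If care leaves the risk mix unchanged and every woman is classified, the adjusted value is 0.78. The article gives no risk share by arm, and the direction can go either way.

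A reader might infer more than the documents support:

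- **That adjustment would turn a benefit into apparent harm.** A simulation can be built to show this, with a true effect of −1.0 point becoming +1.0. It requires no direct effect of care on caesarean and a strong unmeasured cause. A distortion of that size would not overturn the planned difference of 6.5 points (29.4 − 22.9).
- **That women without labour will be dropped.** The article only leaves their category unstated, and it defers full risk definitions to the publication of the study.
- **That unblinded staff assign the risk status.** No section says who assigns it. Allocation is open, but Interim Analysis states an intention to try to blind outcome assessment.

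Finally, outcomes in women at risk when labour starts are a legitimate clinical question. They are not a randomised comparison, and should be labelled accordingly.

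**Conclusion.** The rule is wrong as written. It selects a post-randomisation variable and explicitly rejects the baseline one. The risk-controlled estimate of the total effect and the labour-onset neonatal objective are open to bias of unknown size and direction; the unadjusted intention-to-treat relative risk is not.

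Under the first illustration's assumptions, a planned relative risk of 0.78 is reported as anything from 0.74 to 0.86 as the caseload share runs from 55% to 40%, with power from about 95% to 42% and no distortion at 50%. Apart from 29.4%, 22.9% and 750 per arm, the inputs to the illustrations are assumed. They show sensitivity and do not predict the result.

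**What to change.** Name the primary analysis: either the unadjusted comparison of all randomised women, or one adjusted only for risk at enrolment. The enrolment classification can apply the same ACM criteria to data already planned, since Group Allocation says that "baseline demographic and medical information will be collected from the medical record at the time of entry into the study". Do not adjust the primary outcomes for risk at labour onset. Report that risk by arm as a descriptive result, and state how women with no labour are categorised in it.

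In Aims and Objectives, define the neonatal subgroup by risk at enrolment, or keep the labour-onset comparison and label it non-randomised and exploratory.

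The cost is a change of wording and the coding of existing records, with no extra women. The downside is that fewer women will be in the risk group at enrolment, so that subgroup will be estimated less precisely.
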